## Abstract

**Background:**

The societal costs associated with juvenile delinquency and reoffending are high, emphasising the need for effective prevention strategies. A promising approach is Youth-Initiated Mentoring (YIM). In YIM, professionals support youths in selecting a non-parental adult from within their social network as their mentor. However, until now, little (quasi-)experimental research has been conducted on YIM in the field of juvenile delinquency. We will examine the effectiveness, working mechanisms, and implementation of YIM as a selective prevention strategy for juvenile delinquents.

**Methods:**

This multiple-methods study consists of a quasi-experimental trial and a qualitative study. In the quasi-experimental trial, we aim to include 300 juvenile offenders referred to Halt, a Dutch juvenile justice system organisation which offers youths a diversion program. In the Netherlands, all juvenile offenders between 12 and 18 years old are referred to Halt, where they must complete the Halt intervention. Youths will be non-randomly assigned to region-matched non-YIM-trained and YIM-trained Halt professionals implementing Care as Usual (CAU, i.e., the Halt intervention) or CAU plus YIM, respectively. Despite non-random allocation, this approach may yield comparable conditions regarding (1) the characteristics of professionals delivering the intervention and (2) case type and severity. Youth and caregiver(s) self-report data will be collected at pre-and post-test and a 6-month follow-up and complemented with official Halt records data. Multilevel analyses will test whether youths following CAU plus YIM show a stronger increase in resilience factors and a stronger decline in the need for formal support and delinquency than youths following CAU. In the qualitative study, we will organise focus group interviews with YIM-trained professionals to explore boosters and barriers experienced by professionals during the implementation of YIM.

**Discussion:**

The proposed study will help identify the effectiveness of YIM in strengthening resilience factors and possibly decreasing juvenile delinquency. In addition, it may offer insights into how and for whom YIM works. Finally, this study can help strengthen the implementation of YIM in the future.

**Trial Registration:**

ClinicalTrials.Gov (# NCT05555472). Registered 7 September 2022. https://www.clinicaltrials.gov/ct2/show/NCT05555472?cond=Youth+Initiated+Mentoring&draw=2&rank=1.

## Introduction

Juvenile delinquency, defined as participating in unlawful behaviour as a minor or individual under statutory age, is highly prevalent during adolescence. In 2020, one-third of Dutch adolescents (36.6%) reported having committed at least one crime over the past year (Van der Laan & Beerthuizen, 2021), varying from vandalism to shoplifting to more severe forms of delinquency, such as fighting and threatening others with a weapon. Even though the development of adolescent delinquency follows an age-crime curve, with an upsurge and peak at 17 and a decline thereafter (Moffitt, 1993), about 34–45% of juvenile delinquents reoffends (Beerthuizen & Prop, 2021; Youth Justice Board, 2022). Moreover, the societal costs associated with juvenile delinquency and reoffending are high. Specifically, taking victim costs, criminal justice costs (e.g., police, legal aid, interventions), and loss of societal productivity into account, the costs associated with engaging in a lifelong criminal career may range from $1.7 to $5.3 million per person (e.g., Cohen, 1998; Cohen & Piquero, 2009; Koegl & Day, 2018), and the costs for reoffending by minors can go up to £1.5 billion (Newton et al., 2019). Over the past decades, the trend of “harsh” penal measures has strained governmental budgets while it has failed to reduce reoffending (Andrews & Bonta, 2010). Evidence suggests that early prevention efforts to avert criminal careers are more cost-effective than punitive measures (Welsh & Farrington, 2011, 2012). Consequently, it is crucial to intervene at an early stage of adolescents’ potential criminal careers and of utmost importance to develop interventions to prevent more persistent and violent patterns of delinquent behaviour.

Building effective interventions and prevention programs depends on identifying individual, familial and environmental risk factors linked to heightened delinquent behaviour (Farrington & Welsh, 2007; Nation et al., 2003). Several known key dynamic risk factors for reoffending, also known as *criminogenic needs*, are pro-criminal attitudes, aggressive behaviour, alcohol and drug use, education and employment, leisure and recreation, antisocial peers, and familial risk factors (e.g., Andrews & Bonta, 2010; Assink et al., 2015). Interventions targeting these criminogenic needs are believed to be most effective in reducing reoffending (Andrews & Bonta, 2010; Seigle et al., 2014). Thus, when turning to action-oriented prevention, one should primarily focus on strengthening factors that build resilience and, in turn, desistance against delinquent behaviour, such as increasing involvement with education, employment, leisure, or recreation and building positive relationships with family, peers and others within the social network (e.g., Fergus & Zimmerman, 2005; Seigle et al., 2014; Stagner & Lansing, 2009; Ward & Stewart, 2003; Zimmerman, 2013). Theoretically, Youth-Initiated Mentoring (YIM) is a promising approach for preventing reoffending because it directly or indirectly strengthens several of these factors (Van Dam & Schwartz, 2020; Schwartz et al., 2013).

## Youth-initiated mentoring

YIM is a novel and innovative approach to *natural* or *informal* mentoring (Van Dam & Schwartz, 2020; Schwartz et al., 2013). In contrast to *formal* mentoring programs, where youth are matched to non-parental adults who volunteer within a non-professional context, such as a school or community program (Raposa et al., 2019), *informal* mentoring programs focus on involving a non-parental adult from within the adolescents’ social network, someone with whom the relationship already *naturally* exists. In YIM, youth have the autonomy to choose their *natural* mentor and to *initiate* the mentoring relationship by asking the natural mentor to be their ‘YIM’. Professionals support this entire procedure of identifying, nominating, and officially positioning the YIM. The function of the YIM is twofold: being a confidant and ally for the youth and a partner to caregivers and professionals (Schwartz et al., 2013). In addition, the YIM is closely involved in shaping the support around the adolescents’ needs. Most importantly, the approach capitalises on the strengths and expertise of formal and informal support systems (Van Dam & Verhulst, 2016).

Strengthening natural mentor-mentee relationships alongside professional involvement has three main benefits over matched mentor-mentee relationships: it is more accessible, durable and empowers the social network. First, it is estimated that about 63–86% of youth can identify a natural mentor (e.g., Dang, 2012; Erickson et al., 2009; Hurd & Zimmerman, 2010; Tucker et al., 2019; Van Dam et al., 2017). This relatively large accessibility could counteract delays typically experienced in formal mentoring due to a larger need and interest in these programs than available volunteer mentors (Raposa et al., 2017; Spencer et al., 2019; Tucker et al., 2019). Second, evidence suggests that youth-initiated relationships are more durable than matched relationships, which increases the likelihood of positive youth outcomes (e.g., Schwartz et al., 2013; Grossman & Rhodes, 2002; Spencer et al., 2016). Approximately 74% of all informal mentors are still involved in the youths’ lives after two years (Van Dam et al., 2017), which could be explained by youths choosing their mentor, contributing to a better mentor-mentee match (Tucker et al., 2019). In contrast, matched mentors and mentees often struggle to form meaningful connections, causing the relationship to end prematurely (e.g., (Grossman et al., 2012; Grossman & Rhodes, 2002). Moreover, youth –particularly those in the juvenile justice system– may be more open to involving a mentor they know and trust (Spencer et al., 2019). Third, strengthening the social network empowers families. Parents who feel supported by their social network experience lower levels of parenting stress and engage in more positive parenting practices, such as monitoring and effective parenting (e.g., Ayala-Nunes et al., 2017; Ghazarian & Roche, 2010; McConnell et al., 2011; Taylor et al., 2015). Consequently, this and the youths’ perception of feeling supported might impact the youths’ behaviour, such as displaying less externalising and delinquent behaviour (e.g., Ghazarian & Roche, 2010; Hagen et al., 2005; Hatch et al., 2020; Wight et al., 2006). Thus, YIM has clear benefits over formal mentoring and has the potential to buffer against the development of juvenile delinquency.

## Youth-initiated mentoring for juvenile delinquents

YIM might be particularly well-suited for adolescents in the juvenile justice system (Spencer et al., 2019) because it relies heavily on three basic human needs that could be linked to the development of delinquent behaviour. Specifically, YIM has its theoretical underpinnings in the self-determination theory (Deci & Ryan, 2000), which holds that motivation to learn and develop occurs when an individual fulfils these three basic human needs: the need for autonomy, the need for relatedness, and the need for competence. These needs can be linked to several criminological theories on why youths engage in delinquent behaviour (Moffitt, 1993; Hirschi, 2017; Agnew, 2001, 2017). The overall assumption is that when these needs are met, delinquency in youth dissipates or decreases.

The need for autonomy implies that one feels the need to be a self-governing agent, the “desire to self-organize experience and behavior and to have activity be concordant with one’s integrated sense of self” (Deci & Ryan, 2000, p. 231). Both dual taxonomy theory (Moffitt, 1993) and strain theory (Agnew, 2001, 2017) argue that adolescents’ lack of perceived autonomy encourages delinquent behaviour. During adolescence, adolescents experience a mismatch between their desired and actual autonomy. The strain theory suggests that this ‘strain’ leads to frustration, leading individuals to cope with delinquent behaviour (Agnew, 2001, 2017). Empirical research supports the relationship between the need for autonomy and delinquency (e.g., Brezina, 2008; Van Petegem et al., 2015; Chen, 2010). YIM addresses this need for autonomy by letting the adolescent choose and ask their mentor themselves and working on self-concordant goals (i.e., goals aligned with one’s integrated sense of self) (Ruig & Van Dam, 2021).

The need for relatedness refers to how an individual experiences a sense of belonging and connections with important others (Deci & Ryan, 2000). The social control theory states that stronger bonds with society prevent individuals from engaging in delinquent behaviour (Hirschi, 2017). These bonds express themselves in four factors: (1) *attachment* (i.e., connections with significant others), (2) *involvement* (i.e., engagement in prosocial activities); (3) *commitment* (i.e., degree of connection to society), and (4) *beliefs* (i.e., the value someone places on the norms and values of the society). YIM enhances *attachment* and *commitment* by strengthening relationships with an important person from the social network. YIM might, therefore, impact youths’ degree of perceived social support and their perceived mattering by the active agreement and commitment of this significant other to be their mentor. YIM might also increase *involvement* because involvement in free-time activities, such as hobbies, organisations or clubs, and religious services, has been linked to an increased likelihood of having a natural mentor (Thompson & Greeson, 2017). The YIM could function as a role model for engaging in these prosocial activities as well as prosocial behaviours, but also in cultivating prosocial *beliefs.* Thus, YIM is likely to increase relatedness, which could lead to a decrease in delinquent behaviour.

The need for competence implies that an individual feels capable and effective in their behaviour (Deci & Ryan, 2000). The social learning theory of crime states that both conforming and deviant behaviour can be stimulated via social interactions, modelling, and reinforcement of the displayed behaviour (Akers, 2002). Specifically, the probability of engaging in delinquent behaviour increases when individuals associate with deviant or criminal individuals who either engage in criminal behaviour or have a pro-criminal attitude. Conversely, if one associates with individuals who display prosocial behaviour, one’s behaviour will likely shift in that direction (Akers, 2002). While more of an indirect effect, mentors might model and reinforce adolescents’ need for competence. The YIM could be a role model by providing guidance, sharing moral beliefs and skills, and reinforcing the youths’ self-esteem and prosocial behaviour. Research indicates that youths view their natural mentor as a “powerful role model” (Greeson et al., 2015; Spencer et al., 2016). In addition, YIM actively supports youths’ competence because youths are perceived and considered competent by professionals when choosing their mentors. Consequently, they feel competent to approach someone when help is needed in future situations (Van Dam & Verhulst, 2016; Ruig & Van Dam, 2021). To conclude, YIM might potentially, directly and indirectly, strengthen factors that build resilience and, in turn, desistance against delinquent behaviour.

## Effectiveness of youth-initiated mentoring

Even though YIM is relatively new and rigorous research on the approach has been limited, YIM has been identified as a promising strategy for the future of youth mentoring (Cavell et al., 2021). A recent scoping review on YIM identified nine peer-reviewed studies on the outcomes of YIM (Dantzer & Perry, 2022). YIM has been shown to impact positive youth outcomes, like improved psychological well-being, strengthened relationships, achievement of educational and occupational goals, and strengthened partnerships to support youth adjusting to independent living. These positive outcomes were observed in various vulnerable groups, such as youths who dropped out of high school, youths from multi-problem families receiving youth care, youths at risk for out-of-home-placement, and youths in foster care (e.g., Koper et al., 2021; Schwartz et al., 2013; Spencer et al., 2018; Van Dam et al., 2017). However, it should be noted that no strong conclusions can be drawn about the effectiveness of YIM, as seven out of nine studies adopted a qualitative study design, and none adopted a (quasi-)experimental study design. Moreover, the review only included studies explicitly using the term ‘Youth-Initiated Mentoring’. Noteworthy is that authors identified other studies on youth mentoring approaches that emphasise youths’ voice and choice of a mentor (e.g., C.A.R.E. or Connected Scholars) (Dantzer & Perry, 2022). A recent meta-analysis that included YIM and these similar approaches demonstrated that these approaches showed greater positive effect sizes on positive youth outcomes, such as academic functioning and social-emotional development, compared to formal mentoring approaches or the mere presence of a natural mentor (Van Dam et al., 2021).

Regarding delinquency, however, the findings of (similar) YIM approaches have been mixed. Some evidence suggests a decrease in the likelihood of conviction and engagement in delinquent activities (Millenky et al., 2010; Schwartz et al., 2013). At the same time, other studies indicate that these similar approaches have no impact on officially registered and self-reported delinquency nor delinquency-related outcomes, such as cognitive distortions, aggressive behaviour, substance use, and parenting behaviours (James et al., 2016; de Vries et al., 2017; De Vries et al., 2018). In conclusion, there is a need for (quasi-)experimental studies on the effectiveness of YIM in the field of juvenile delinquency. This offers the opportunity to determine whether YIM effectively or strengthens resilience factors and halts or reduces juvenile delinquency.

## The present study

Even though YIM seems particularly well-suited for use in a population of juvenile delinquents; currently, little is known about its effectiveness in the field of juvenile delinquency. Moreover, knowledge of mediators and moderators of potential YIM effects has yet to be documented. In addition, gaining insight into professionals’ experience implementing YIM is essential. In our multiple-methods multi-informant study, we will target these three main questions about the effectiveness (“Does YIM work?”), possible working mechanisms (“How does YIM work? And for whom does YIM work?”) and the implementation process (“What are boosters and barriers in the implementation of YIM?”). Our quasi-experimental trial will answer the first two questions, and our qualitative study will answer the last.

Concerning effectiveness, we expect that YIM will strengthen youth resilience factors, such as perceived social support and social resourcefulness (*primary outcomes*), relatedness to others, autonomy, and competence. Moreover, we expect YIM to contribute to halting or decreasing the need for (formal) support and self-reported delinquency (*secondary outcomes*). Concerning the working mechanisms of YIM, we expect that an increase in resilience factors mediates the effect of halting or decreasing the need for (formal) support and self-reported delinquency. Furthermore, the impact of YIM will be larger for some individuals than for others, based on moderators such as demographic factors, psychosocial problems, mentor-mentee relationship quality (e.g., type of support, frequency of contact, relationship duration, (non)kin), peer network quality, parental monitoring, and treatment characteristics (i.e., Halt intervention characteristics and YIM characteristics). Also, see Fig. 1 for a pictorial depiction of the theoretical model. Finally, concerning the implementation of YIM, we will explore the boosters and barriers that facilitate or prevent its successful implementation. We intend to explore boosters and barriers within three domains: the innovation domain (i.e., characteristics of the innovation being implemented: YIM), the individuals’ domain (i.e., characteristics of individuals receiving the innovation: youth and caregivers, and characteristics of individuals delivering the innovation: Halt professionals) and the inner setting domain (i.e., characteristics of the setting in which the innovation is being implemented: Halt) (Damschroder et al., 2009, 2022; Fleuren et al., 2014).

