#### Materials

Our primary outcome, with which we will assess the main intervention effect of YIM on perceived social support and social resourcefulness, will be measured with the Berlin Social Support Scales (BSSS), respectively the subscales ‘Perceived Social Support’ and ‘Support Seeking’ (Schwarzer & Schulz, 2003). All youth and caregiver(s)’ outcomes and measurement points are depicted in Table 1. In Table 2, an overview of measures administered to Halt professionals is presented.

**Table 1 Tab1:** Overview of Youth and Caregiver(s) Measurements

Concepts		Measurement	Informants	# of items	Baseline	Post-test	Follow-up
Demographic factors		Demographics	Y	18–21	*****		
Offense and referral information		Halt’s registration system	HP	-	*****		
Halt intervention characteristics		Halt’s registration system	HP	-	*****		
YIM characteristics		Halt’s registration system	HP	-		*****	
Dynamic risk factors		Halt-SI	HP	-	*****		
Psychosocial problems		Halt-SI SDQ	HP Y	- 20	***** *****		
Prosocial behaviour		SDQ	Y	5	*****	*****	*****

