**Power Analysis.** To assess the sample size per condition for the primary and secondary outcomes, we performed an a priori power analysis in G*Power 3.1 (Faul et al., 2009). To attain a power level of 0.80 with a significance level of α = 0.05, a total sample size of *N* = 100 is necessary to detect a small effect size (*f* = 0.10) in a linear multiple regression analysis. Meta-analyses that explored the effects of formal mentoring programs on delinquent behaviour and reoffending revealed small overall effects, both *d* = 0.21 (~ f = 0.10) (Jolliffe & Farrington, 2007; Tolan et al., 2014). For moderator and mediator analysis, a larger sample size is required. We performed a priori power analysis a Monte Carlo Power Analysis (Schoemann et al., 2017, p. 384). For a simple trivariate correlation, a total sample size of *N* = 150 is necessary to attain a power level of 0.80 with a significance level of α = 0.05. This would indicate *N* = 75 per condition. However, we aim to include *N* = 150 per condition because (1) we will also include time as a factor in the moderator and mediation models, and (2) we expect relatively high drop-out rates of over 20% (e.g., drop-out at post-test or follow-up measurements) (Furlan et al., 2009).

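### The 80% power stated for the primary outcomes is supported only by a formal-mentoring effect on delinquency, and the design does not deliver it at that effect for any outcome

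*Protocol article*

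**What the plan says.** The section The present study names the primary outcomes in its first hypothesis: "we expect that YIM will strengthen youth resilience factors, such as perceived social support and social resourcefulness". Need for formal support and self-reported delinquency are labelled secondary in the next sentence. Materials ties the two primary outcomes to the BSSS subscales for perceived support and support seeking.

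The Power Analysis paragraph under Data analyses (Study 1) opens with its scope: "To assess the sample size per condition for the primary and secondary outcomes". It then states that 100 youths in total give power 0.80 at α = 0.05 for a small effect, f = 0.10, in linear multiple regression. The evidence offered is "Meta-analyses that explored the effects of formal mentoring programs on delinquent behaviour and reoffending revealed small overall effects", with d = 0.21 equated to f = 0.10. No effect on perceived support or support seeking is given there or elsewhere in the article.

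The recruitment target is 150 per condition. The paragraph explains it by a separate mediation and moderation calculation (150 in total), by time entering those models, and by expected drop-out of over 20%.

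**The concern.** Two things are wrong with the power statement.

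First, its scope and its evidence do not match. It is said to cover the primary outcomes, but the cited effect belongs to a secondary outcome and to a type of programme that the article itself contrasts with Youth-Initiated Mentoring (YIM). A reader cannot tell why a small standardised effect of this size is the right planning value for the BSSS subscales.

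Second, the stated sample size does not follow from the stated effect, whichever outcome is meant. Correcting only the evidence would leave a wrong figure in place. Correcting only the figure would leave an effect without justification for the primary outcomes.

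At stake is how the results are read. Someone who trusts the 80% would take a non-significant primary result as informative about effects near d = 0.21, when the trial would miss such an effect more often than not in the unadjusted comparison.

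**Working it through.** **Inputs from the Protocol article:** power 0.80; α = 0.05 (taken as two-sided); f = 0.10, equated with d = 0.21; stated total of 100; planned 300 in two equal groups; drop-out over 20%, so at most 300 × 0.8 = 240 completers; 31 + 31 = 62 professionals; regression on baseline outcome and condition.

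**Assumptions not in the article:** baseline–outcome correlation r = 0.5 and professional-level intraclass correlation (ICC) = 0.05, each shown beside the value 0.

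**1. Reproducing the stated total of 100.** Power comes from the noncentral F distribution with noncentrality f² × N. With two equal groups f = d/2, so d = 0.21 gives f = 0.105 and f² = 0.011.

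| Effect entered | Predictors tested | N for 80% power | Power at N = 100 |
|---|---|---|---|
| f² = 0.01 (f = 0.10) | 1 | 787 | 16.8% |
| f² = 0.01 | 2 | 967 | 13.0% |
| f² = 0.011 (d = 0.21) | 1 | 714 | 18.0% |
| f² = 0.02 | 1 | 395 | 28.8% |
| f² = 0.10 | 1 | 81 | 87.9% |
| f² = 0.10 | 2 | **100** | 80.3% |
| f² = 0.10 | 3 | 114 | 74.2% |

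A one-sided test at f = 0.10 needs 620. Of the variants tried, only f² = 0.10 with two tested predictors returns 100. That is f = √0.10 ≈ 0.32, or d ≈ 0.63, three times the cited 0.21. That 0.10 was entered as f² is an inference from this match; the article does not say so.

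**2. Power at the cited effect.** For n per group, power ≈ Φ(d × √(n/2) − 1.96).

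- 50 per group: 0.21 × 5.000 − 1.96 = −0.91, power 18%.
- 150 per group: 0.21 × 8.660 − 1.96 = −0.14, power 44%.
- 120 per group: 0.21 × 7.746 − 1.96 = −0.33, power 37%.

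With r = 0.5, d is divided by √(1 − 0.25) = 0.866, giving 56% (300 youths) and 47% (240). With ICC = 0.05 and no baseline adjustment the figures are 38% and 33%. Even with r = 0.7 and no clustering they are 72% and 63%.

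**3. Detectable effect at 80% power.** d = (1.960 + 0.842) × 2/√N × √(1 − r²) × √DE, where the design effect is DE = 1 + (N/62 − 1) × ICC.

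- N = 300: N/62 = 4.84, so DE = 1.192 at ICC = 0.05.
- N = 240: N/62 = 3.87, so DE = 1.144 at ICC = 0.05.

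| N | r = 0, ICC = 0 | r = 0.5, ICC = 0 | r = 0, ICC = 0.05 | r = 0.5, ICC = 0.05 |
|---|---|---|---|---|
| 300 | 0.323 | 0.280 | 0.353 | 0.306 |
| 240 | 0.362 | 0.313 | 0.387 | 0.335 |

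Relative to the cited effect, this runs from 0.280/0.21 = 1.3 to 0.387/0.21 = 1.8 times d = 0.21.

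**The case against.** The strongest reply has four parts, and each limits what can be said.

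- **An effect was assumed for the primary outcomes.** The paragraph applies f = 0.10 to both tiers. Power is always conditional on an assumed effect, and a small standardised effect is a usable planning value. A reader might infer that the power for the primary tests has no basis at all. The article does not support that; what it lacks is evidence specific to the BSSS outcomes.
- **The borrowed value may be cautious.** The section on effectiveness says of YIM-like programmes that "these approaches showed greater positive effect sizes on positive youth outcomes, such as academic functioning and social-emotional development, compared to formal mentoring approaches". That points to larger rather than smaller effects on social-emotional outcomes. It gives no figure, however, and does not name perceived support or support seeking. It therefore neither rescues the 80% nor supplies a replacement effect.
- **The target of 300 is not derived from d = 0.21.** A reader might infer that the whole sample size rests on the delinquency effect. It does not: that calculation gives only the total of 100, and the 300 is justified by the mediation calculation, time and drop-out. The fault lies in the power claim.
- **The source mismatch is not what breaks the 80%.** The shortfall would be the same had d = 0.21 come from a perfectly matched social-support trial. This is correct, and it is why the arithmetic has to be part of the point.

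For delinquency, the article reports that "other studies indicate that these similar approaches have no impact on officially registered and self-reported delinquency", but beside other studies that found decreases. Mixed evidence does not show d = 0.21 to be implausible there. Nor does the article plan to read a null delinquency result as evidence against YIM; it urges caution about causal conclusions.

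**Conclusion.** The point holds in a limited form. The Power Analysis paragraph states 80% power for primary and secondary outcomes at an effect supported only by formal-mentoring evidence on delinquency, and the stated power is not delivered at that effect for any outcome. Unadjusted, it is about 17–18% with 100 youths, 44% with 300 and 37% with 240 completers.

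The 300 youths can detect d of about 0.28 to 0.35 with 80% power, and 240 completers about 0.31 to 0.39, over the assumed values of r (0 or 0.5) and ICC (0 or 0.05). Because drop-out is expected to exceed 20%, 240 is an upper bound on completers.

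Whether the trial is adequately powered for the BSSS outcomes cannot be settled from the article, because it gives no expected effect for them.

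**What to change.** Reword the Power Analysis paragraph in two places.

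1. State that d = 0.21 comes from meta-analyses of formal mentoring on delinquency, and so relates to a secondary outcome.
2. Replace the 80% power claim for the two primary BSSS outcomes with the effect detectable at 80% power, two-sided 5%: d of about 0.32 with 300 youths and 0.36 with 240, unadjusted; 0.28 and 0.31 with an assumed baseline correlation of 0.5; and 0.306 to 0.353 (300) and 0.335 to 0.387 (240) once an assumed professional ICC of 0.05 is added. Label the correlation and the ICC as assumptions. The total of 100 at f = 0.10 should not remain as the basis of a power claim.

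The cost is rewording only. The number of participants, the outcomes and the analysis model stay as they are. The downside is a less favourable power statement than the present one.
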